## Abstract

**Background:**

The consumption of edible oils in China has increased rapidly in recent years, and the total amount of edible-oil intake in the country has ranked first in the world. The choice and intake of edible oils, as a source of fats, are important factors that affect people’s health. Many chronic diseases are closely associated with high-calorie and saturated-fat intake. The influence of traditional concepts that promote the use of edible oils among women, particularly housewives, plays a key role in a household’s diet and nutrition because the diet-related knowledge, attitude and behaviour of housewives are dominant factors in planning and preparing their family’s meals. WeChat, which was developed by Tencent, is a multipurpose messaging, social media and mobile payment application (app) in China. Described by Forbes as one of the world’s most powerful apps, WeChat provides considerable convenience in disseminating knowledge. Accordingly, this study aims to design a pilot intervention to decrease the use of edible oils in Chinese households. The intervention, which is based on theories of behaviour change, will be implemented through WeChat.

**Design and methods:**

The study design is a randomised controlled trial that adopts knowledge, attitude and practice, social cognitive and stages of change theories as theoretical models. A total of 800 housewives between the ages of 25 and 45 years will be recruited on WeChat and from the communities in four areas (including rural and urban) in Chongqing, China. A self-administered questionnaire will be used to collect information regarding age, educational level, occupation, family members, edible-oil intake habits, knowledge of edible oils and WeChat usage habits. A total of 200 participants will be selected and randomly assigned to two equal-sized groups: group A (the intervention group) and group B (the control group). Group A will receive health education regarding edible oils for four consecutive weeks, whereas group B will be treated as the blank control. Each participant will complete a battery of knowledge, attitude and behaviour tests immediately, 3 months and 6 months after the intervention. In addition, weight, moisture rate, fat rate, visceral fat level and body mass index will be calculated using a multifunctional weighing scale, namely, Tanita BC-601 (Japan). The study is currently in the design stage.

**Discussion:**

This study aims to increase knowledge and awareness of the appropriate use of edible oils, thereby encouraging participants to change behaviour by decreasing the intake of unhealthy levels of edible oils. It will be the first intervention to investigate the use of edible oils in China through WeChat. We predict that receiving health education regarding edible oils through WeChat will substantially improve the knowledge and attitude of the respondents. The members of the intervention group will have increased awareness and will be willing to decrease their use of edible oils to remain healthy. Results of this study may provide scientific evidence for the effect of health education through WeChat on edible oil-intake behaviour, thereby offering a comprehensive intervention to decrease the use of edible oils and promote a healthy lifestyle.

**Trial registration:**

Chinese Clinical Trial Registry (primary registry in the World Health Organisation registry network): ChiCTR-IOR-17013472. Registered on 21 November 2017.

**Electronic supplementary material:**

The online version of this article (10.1186/s13063-018-3015-7) contains supplementary material, which is available to authorized users.

## Background

Edible oils are important sources of energy and essential fatty acids for the human body. An appropriate amount of edible-oil intake can provide humans with various types of fatty acids and accelerate the absorption of fat-soluble vitamins [1]. Nutritional, biological, clinical and medical studies postulate that fatty acids in edible oils play an important role in maintaining human health [2, 3]. For example, omega-3 fatty acids, which are polyunsaturated fatty acids, can promote the reduction of triglycerides and be beneficial for cardiac health. Studies have found that an inadequate intake of omega-3 fatty acids is a risk factor for many nutrition-related diseases [4]. Furthermore, the excessive consumption of edible oils will lead to too much calorie intake, which may be linked to various negative health consequences, such as obesity, diabetes and other chronic diseases, according to a previous study [5].

Edible-oil intake and dietary habits play crucial roles in human health [1]. At present, however, local and overseas studies on edible oils provide conflicting results. The Centres for Disease Control and Prevention reported that over one third of adults in the United States (approximately 78 million people) are suffering from obesity. The 2015–2020 Dietary Guidelines for Americans recommend that consuming low-fat dairy helps control fat intake [6, 7]. The obesity rate in Japan is extremely low compared with that in Europe and the United States, one of the important reasons is that Japanese people have less oil intake [8]. The World Health Organisation recommends that total fat intake should not exceed 30% of the total energy intake to avoid unhealthy weight gain [9]. Evidence indicates that oil intake in the Chinese diet is significantly beyond the standard. The per capita oil intake among Chinese reaches 42 g, which is considerably higher than the recommended 25 g; such excessive intake has become a major health obstacle [6, 10]. At present, the major types of edible oils in China are soybean oil, rapeseed oil and peanut oil, supplemented by animal oil; differences in oil intake have been observed among various populations and regions [11, 12]. For example, edible-oil intake is higher among men than among women [13]. Rural residents mostly use rapeseed oil, whereas rapeseed oil consumption is relatively low in urban areas [14]. Furthermore, Chinese people tend to prefer refined edible oils, which lack trace elements due to excessive refining, and thus, negatively affect immunity and health [1, 15].

Housewives are key figures in the current study. In China, women pay more attention to their family’s diet and nutrition than men, and as influenced by traditional ideas, housework is primarily the women’s duty [16]. At present, full-time housewives are not as common as before, particularly in larger cities and other urban areas [17]. Modern women seek employment not only to earn money to support their family but also for self-improvement. Accordingly, the housewives referred to in this study are women who play a key role in housework, particularly in cooking, in addition to their jobs. Besides, the knowledge, attitude and behaviour of women regarding nutrition also affect their children’s growth and health [18] because women play a dominant role in determining the diet and nutrition of their family [19]. However, no study has yet investigated the knowledge and attitude of Chinese housewives regarding edible oils or has intervened on their edible-oil intake behaviour. Therefore, the knowledge and attitude of housewives regarding excessive edible-oil intake should be assessed to promote healthy behaviour in choosing edible oils.

In recent years, China has witnessed an unprecedented increase in the use of social media. WeChat, which was released in January 2011, is a mobile communication tool developed by Tencent in China. WeChat is one of the leading social networks worldwide, ranking fifth in terms of the number of active users. As of 2018, it is one of the world’s largest stand-alone mobile apps, with over one billion monthly active users (902 million daily active users) [20]. WeChat has been dubbed China’s ‘app for everything’ and a ‘super app’ because of its wide range of functions and platforms. For comparison, Facebook Messenger and WhatsApp Messenger (two competitive international messaging services that are popular in the West) have approximately one billion monthly active users in 2017 but did not offer most of the other services available on WeChat [21]. WeChat exhibits a mass media feature, which can quickly send voice messages, videos, pictures and texts and allows repeatable views. Consequently, effective education can be provided at any time through WeChat, thereby saving considerable material resources. In addition, the Internet provides timely information and new features to attract respondents. Considering the aforementioned advantages of WeChat, we hypothesise that respondents will be more willing to participate in the project if WeChat is used than if traditional methods for delivering intervention are used. Hence, we speculate that this online method may reduce the dropout rate of respondents.

At present, public awareness of the risks of excessive oil consumption is weak, and most housewives lack the necessary knowledge regarding appropriate amounts of edible-oil intake [22]. Although numerous health information sources are readily available, distinguishing the authenticity of information is generally difficult given that some sources provide erroneous information. Most studies [23–25] have analysed the ingredients of edible oils and have investigated their pathogenic mechanism in various diseases. However, surveys on public cognition and factors associated with edible oils remain limited. Thus, decreasing the use of edible oils should be explored, particularly under the current condition of increased consumption. Moreover, a scientific dissemination platform on WeChat may be used as a nutritional education carrier, which is urgently needed. Furthermore, considering its enormous number of users, WeChat may become an effective intervention tool for decreasing the use of edible oils among households.

## Methods and analysis

### Study design

This study has three phases. First, 800 participants will be recruited from different communities to answer the status survey questionnaire, which allows us to obtain information regarding the current consumption of edible oils and the use of WeChat. Subsequently, 200 participants will be selected from the status survey. After the baseline survey, participants who met the inclusion criteria and provided demographic information will be randomly divided following a 1:1 ratio to an intervention group and a control group using computerised simple randomisation in SPSS. An intervention will then be performed on the intervention group for 4 weeks. Afterwards, tests will be conducted on each group immediately, 3 months and 6 months after the intervention. Furthermore, after 6 months of follow-up, the control group will be provided with the same information given to the intervention group to raise the awareness of its members regarding the need to reduce their edible-oil intake. This study has been registered at the Chinese Clinical Trials Registry (ChiCTR-IOR-17013472). Figure 1 shows the research design. Figure 2 shows the schedule of enrolment, assessment and intervention. Additional file 1 provides the complete Standard Protocol Items: Recommendations for Standard Protocol Items: Recommendations for Interventional Trials (SPIRIT) Checklist.

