### Participants and recruitment

Participants will be recruited from the following four areas (rural and urban) in Chongqing, China: Yuzhong District, Shapingba District, Dianjiang District and Wulong District. Each district represents a different level of economic development.

A publicity group will be set up during the early stage of the project. An advertisement with a short comic strip will be designed to present the study, and printed posters and leaflets will be disseminated in the cooperating communities. Women who are interested can register at the community centre. Community leaders can, if they find it appropriate, inform them about the possibility of participating in the study. Recruitment will also be done through announcements on microblogs and WeChat. Women who wish to participate will have to provide their informed consent and enrol on the study’s homepage if they meet the inclusion criteria.

The inclusion criteria are as follows: women who are between the ages of 25 and 45 years, involved mainly in housework (particularly cooking) and active daily users of WeChat (i.e. using WeChat more than three times daily).

The exclusion criteria are as follows: individuals who have never cooked, have been involved in other edible-oil experiments and those with cognitive or verbal impairments or diseases that require them to follow strict diets.

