### Study procedure

This study uses a combination of primary and secondary data. The quantitative cross-sectional studies will last for 4 weeks and will use WeChat as an intervention tool. A total of 800 housewives between the ages of 25 to 45 years will be recruited from different communities in Chongqing, China. A status survey will be conducted from September 2019 to November 2019. A previous study [36] has proven that age and education are associated with edible-oil intake behaviour. To eliminate the influence of confounding factors, 200 housewives with similar ages and educational levels will be selected to participate in a baseline survey. Subsequently, they will be divided randomly following a 1:1 ratio into an intervention group (group A) and a control group (group B) using computerised simple randomisation in SPSS. In the next 4 weeks, group A will receive health education through WeChat every 2 days, whereas group B will receive nothing. Each participant will then be given knowledge, attitude and behaviour tests immediately (immediate effect), 3 months (short-term effect) and 6 months (long-term effect) after the intervention. In accordance with the SOC model [35], the entire process of changing edible-oil intake behaviour among the housewives will be divided into six stages (Table 1). In addition, the changes in their behaviour stages and influencing factors will be analysed to evaluate the effects of the intervention on edible-oil intake. All subjects will read and sign a written informed consent form before their voluntary participation.

**Table 1 Tab1:** Description of intervention methods corresponding to different stages

Stages	Intervention focus
Precontemplation	Spread the knowledge and benefits related to healthy oils
Contemplation	Encourage them to start trying to control oil intake
Preparation	Guide participants on how to use edible oils in a healthy manner
Action	Help participants identify factors that affect their persistence in decreasing oil intake
Maintenance	Self-motivation
Termination	\

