## Discussion

In accordance with the experiment design, the intervention group will receive 4 weeks of intervention to determine whether differences in edible-oil knowledge and intake behaviour exist between the intervention group and the control group. The experimental design will ensure balance among the confounding variables in each group and will eliminate the bias caused by the characteristics of the participants. Given that the enrolled participants should be good at using the WeChat app, the samples will exhibit this bias from the beginning. To avoid potential biases during the entire process, we will strictly follow the inclusion criteria when recruiting participants and use blind methods to collect data during the implementation phase. In addition, to increase the participation rate and reduce the selection bias, we will use children’s health as an entry point. Given that the participants are women between the ages of 25 to 45 years, most of them will have children in their family. In China, children are considered ‘emperors’ in the family. Most women care about their children’s health; thus, we will provide knowledge about edible-oil consumption among children during the intervention.

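### The protocol names simple randomisation, which cannot guarantee the equal-sized groups or the ensured balance it claims, and allocation takes no account of the four districts

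*Protocol article*

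**What the plan says.** The Study design section has participants divided 1:1 into an intervention group and a "control group using computerised simple randomisation in SPSS". The Study procedure section repeats the method: "and a control group (group B) using computerised simple randomisation in SPSS". Neither place mentions blocks or strata. Randomisation and blinding adds that the study coordinator checks the computer-generated assignments with a randomisation table.

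The Abstract (Design and methods) describes the result as equal arms: "A total of 200 participants will be selected and randomly assigned to two equal-sized groups". The Discussion goes further: "The experimental design will ensure balance among the confounding variables in each group and will eliminate the bias" that participant characteristics would cause.

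Before allocation, confounding is handled by selection: "To eliminate the influence of confounding factors, 200 housewives with similar ages and educational levels will be selected".

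Recruitment covers four rural and urban areas of Chongqing, and the protocol says of them: "Each district represents a different level of economic development". The Background notes that "differences in oil intake have been observed among various populations and regions", and the Discussion speculates that economic status may influence oil use.

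**The concern.** Simple randomisation is an independent draw for each person. It fixes neither the arm sizes nor the distribution of any covariate between the arms. The protocol therefore names a method and credits the design with properties which that method lacks.

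The selection step does not close the gap. It narrows the sample on age and education, but does nothing for district, rural or urban residence, or economic level. These are features the protocol itself treats as differing between recruitment areas and as possibly related to oil use. If the arms differ by district through chance, the observed difference in household oil use is partly a difference between districts, and the allocation does nothing to limit it. Readers of the results would also have been told that such imbalance could not occur.

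**Working it through.** **Inputs.** 200 women, 1:1, simple randomisation (Study design; Study procedure). Two equal groups, so 100:100 (Abstract). Four districts (Participants and recruitment). The protocol gives no numbers per district, so 50 each is assumed.

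**1. Arm sizes.** Under simple randomisation the size of group A is X ~ Binomial(200, 0.5).
- P(X = 100) = C(200,100)/2^200 = 0.0563, or 5.6%. The stated equal split is therefore not a property of the stated method.
- SD of X = √(200 × 0.5 × 0.5) = 7.1.
- P(110:90 or worse) = P(|X − 100| ≥ 10) = 0.179, or 17.9%.
- X lies between 86 and 114 with probability 0.960.

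**2. Cost of unequal arms.** Efficiency relative to 1:1 is 4ab/(a + b)².
- 110:90 gives 4 × 110 × 90/200² = 0.990.
- 114:86 gives 4 × 114 × 86/200² = 0.980.

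Unequal arms alone thus cost about 1% to 2%.

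**3. District balance, independent draws.** Within a district of 50, the number in group A is Binomial(50, 0.5).
- P(30:20 or worse in a given district) = 0.203.
- P(in at least one of four) = 1 − (1 − 0.203)⁴ = 0.596, about 60%.

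**4. District balance, total fixed at 100:100.** The count in one district is then hypergeometric (50 of 200, 100 drawn).
- P(30:20 or worse in a given district) = 0.141.
- P(in at least one of four) = 0.404, about 40%, by enumerating all splits that sum to 100.

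Fixing the total makes the arms equal but leaves the districts to chance.

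**5. What a 30:20 district could do to the result.** This step is illustrative. Assume that district explains 10% to 20% of the variance in oil intake. Assume also that one district splits 30:20 with equal arms, and that the other three share a common mean and absorb the difference. The arms then differ by 0.30 − 0.20 = 0.10 in the share of women from that district.
- District one between-district SD from the overall mean: shift = 0.10 × (4/3) × √0.10 = 0.042 SD, or 0.10 × (4/3) × √0.20 = 0.060 SD. The factor 4/3 arises because the other three districts lie one third as far on the other side of the mean.
- District carrying all of the between-district variance: its deviation is √(3 × R²), so the shift is 0.10 × (4/3) × √0.30 = 0.073 SD, or 0.10 × (4/3) × √0.60 = 0.103 SD.

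The standard error of a mean difference with 100 per arm is √(2/100) = 0.141 SD. On these assumptions the shift is smaller than one standard error.

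**The case against.** The best defence is that the label is loose and the procedure sound. All 200 women are identified first, they are divided 1:1, and a randomisation table is mentioned. A random 100:100 split of a known list fits that text, with simple meaning only unstratified. On this reading the 5.6% and 17.9% fall away. The reading is plausible, but it is not the method named in two sections, so the wording would still need correcting, and the roughly 40% chance of an uneven district would remain.

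A second defence is that the Discussion credits the whole experimental design, including the selection step. That helps for age and education, though similar is not identical. It does not help for district, so the words ensure and eliminate remain unsupported.

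Third, the evidence that district matters is thin. The Background statement is general to China, its rural and urban example concerns type of oil rather than amount, and the remark on economic status is speculation. This stands, and it limits the severity.

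Several stronger conclusions are tempting but are not supported:
- **That the trial would be biased.** Simple randomisation balances district in expectation, and the ordinary unadjusted standard error already allows for chance imbalance.
- **That the treatment-effect model omits district.** The regression under Analysis strategy lists age, occupation and education, but as written it examines factors that influence oil intake, starting from baseline anthropometric measurements. It is not presented as the comparison of group A with group B. The article does not give that model, and its covariates may be set in a document not shown.
- **That selecting women of similar age and education is an error.** Restriction is a recognised design choice that trades generalisability for homogeneity.
- **That stratification would buy a definite gain in power.** Any figure needs an assumed share of variance due to district and an assumed number analysed, and much of the gain would come from covariate adjustment alone.

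**Conclusion.** The point holds in a limited form. Simple randomisation, as named, cannot guarantee two equal groups (5.6% chance of exactly 100:100), and neither it nor the age and education selection can ensure balance on confounders or eliminate bias from participant characteristics. District is left to chance: at least one of four districts would split 30:20 or worse with probability about 60% under independent draws, or about 40% under a fixed 100:100 split. Both figures assume 50 women per district.

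The consequence is modest. The comparison remains valid, unequal arms cost 1% to 2% of efficiency, and under the illustrative assumptions one uneven district moves the result by less than one standard error. This is worth correcting because the claim is wrong as written and the remedy costs little, not because the trial would otherwise fail.

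**What to change.** 1. Replace simple randomisation in Study design and Study procedure with 1:1 permuted blocks stratified by the four districts. All 200 women, and hence their districts, are known before allocation. The arms would then be equal apart from at most one incomplete block per district, and with 50 per district each would split about 25:25. If a fixed 100:100 split without strata was intended, the text should say so and not call it simple randomisation.
2. Include district as a covariate in the comparison of group A with group B, wherever that model is specified.
3. Reword the Discussion sentence to claim balance by design only on the stratification factor, and balance in expectation on everything else.

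The selection on age and education can stay as a design choice. The cost is a slightly more complex allocation list, which the study coordinator can produce, and a few degrees of freedom in the model (three for four districts). No extra visits, staff or data are needed. The Abstract describes the study as still in the design stage, so the change was feasible when the plan was written.
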